## **6. Withdrawal and replacement of subjects**

### **Criteria for withdrawal**

Subjects may prematurely discontinue from the study at any time. Premature discontinuation from the study is to be understood when the subject did not undergo End of Study (EOS) examination and / or all pivotal assessments during the study.

Subjects must be withdrawn under the following circumstances:

- at their own request
- if the investigator feels it would not be in the best interest of the subject to continue
- if the subject violates conditions laid out in the consent form / information sheet or disregards instructions by the study personal

In all cases, the reason why subjects are withdrawn must be recorded in detail in the CRF and in the subject's medical records. Should the study be discontinued prematurely, all study materials (complete, partially completed and empty CRFs) will be retained.

Replacement policy: Dropouts are not included in the sample size and will be replaced by allocation of the next free subject number.

### **Follow-up of patients withdrawn from the study**

In case of premature discontinuation after study drug intake, the investigations scheduled for the EOS visit will be performed within 7 days after study drug discontinuation. The subjects will be advised that participation in these investigations is voluntary. Furthermore, they may request that from the time point of withdrawal no more data will be recorded and that all biological samples collected in the course of the study will be destroyed.

### **Premature termination of the study**

The investigators have the right to close this study at any time. The ethics committee and the competent regulatory authority will be informed within 15 days of early termination.

The trial or single dose steps will be terminated prematurely in the following cases:

- If adverse events occur which are so serious that the risk-benefit ratio is not acceptable.
- If the number of dropouts is so high that proper completion of the trial cannot realistically be expected.

## **7. Study medication**

Active agent and characteristics: Metyrapone

Trade name of the agent: Metycor 250 mg

Supply Chain: Metycor will be provided by HRA pharma. The drug will be stored in accordance with the prescribing information.

IMP administration and handling: Metycor will be taken orally with a dose of 500 mg at 6 p.m. and 250 mg at 10 p.m.

Drug Accountability and assessment of subjects' compliance: Drug accountability and subjects' compliance will be directly observed by the investigators. Additionally, batch numbers will be recorded in the CRF.

Concomitant medication: Concomitant medication will be registered at every study visit.

Randomization and blinding: This study is designed as an open label, single armed trial. No randomization and blinding will be performed.

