#### **4. Outcome parameters:**

##### **Primary outcome parameter:**

- Hepatic lipid content (HCL) assessed by  $^1\text{H}$  magnetic resonance spectroscopy

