##### **Secondary outcome parameters:**

- insulin secretion and sensitivity based on validated indices (HOMA\_IR, CLIX)
- subcutaneous and visceral fat mass, body composition
- Systolic and diastolic heart function, epicardial and pericardial fat mass
- ectopic lipid deposition in the skeletal muscle and the myocardium
- standardized blood pressure measurements (blood pressure for 24h hours and Schellong tests)
- parameters of systemic inflammation (CRP, IL-6, PAI-1, TNF-alpha, homocysteine, leucocytes, monocytes)
- parameters of the Renin-Angiotensin-Aldosterone system (RAAS) activation (RAAS FINGERPRINT®) (18)

- hypercoagulability assessment by thrombin generation assays (TECHNOTHROMBIN ®)
- standardized clinical chronotype evaluation by Munich ChronoType Questionnaire and psychological testing
- body temperature measurements during the day by an actimetry watch
- analyses of peroxiredoxin oxidation cycles from red blood cells (19),
- circadian clock transcript changes from peripheral blood mononuclear cells (20),
- combined untargeted/targeted LC-MS/MS based approaches
- concentrations of testosterone and adrenal androgen precursors
- gender specific differences

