## **5. Methods:**

### **Study design:**

#### **Working plan A (WPA):**

#### **Cardiometabolic phenotyping:**

To address aim 1 we will perform a cross-sectional study in patients, who are in routine care at the endocrine outpatients' clinic for the hormonal work up of an adrenal adenoma. 25 patients with an ACS will be recruited and compared to 25 patients of comparable age and sex with a sufficient suppression of cortisol  $< 1.8$  ug/dl following a 1 mg dexamethasone suppression test.

Experiments will be performed in the morning after an overnight fast. Subjects have to avoid intense physical exercise and consumption of alcoholic beverages for at least 48 hours previous to study related experiments.

$^1\text{H}$  magnetic resonance (MR) spectroscopy measurements will be performed in high field 3T whole body MR system (Magnetom, Siemens Healthcare, Erlangen, Germany) equipped with appropriate surface coils. Ectopic fat in the liver, the skeletal muscle and the myocardium will be assessed by the single voxel localized  $^1\text{H}$  MRS method (41).

After the MR measurements a frequently sampled oral glucose tolerance test will be performed and surrogate parameters of insulin secretion and sensitivity will be

calculated based on validated indices (HOMA\_IR, CLIX, OGIS, IGI, Disposition Index, Adaptation Index) (21).

Additionally, blood will be drawn at baseline for the measurement of parameters of systemic inflammation (CRP, IL-6, PAI-1, TNF-alpha, homocysteine, leucocytes, monocytes), the renin-angiotensin-aldosterone system (RAAS FINGERPRINT ®) and hypercoagulability (TECHNOTHROMBIN ®).

To estimate diurnal cycles of cortisol secretion salivary cortisol will be drawn at 8:00 a.m. and midnight.

To address aim 2, additional blood will be drawn to analyze the peroxiredoxin oxidation cycles from red blood cells (19), as well as the circadian clock transcript changes from peripheral blood mononuclear cells (21).

In addition, blood will be stored for combined untargeted/targeted LC-MS/MS based metabolomic/proteomic approaches.

Overall, 125 ml blood will be drawn in total for all biochemical analyses of WPA.

A systematical assessment of the chronotype will be performed by using the Munich ChronoType Questionnaire. Furthermore, the following psychological tests will be applied:

- Measurement of vigilant attention and impulsivity (by means of the Psychomotor Vigilance Task)
- Implicit association of concepts (by the Implicit Association Test)

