**Working plan B (WPB):**

A subgroup 15 consecutive patients, who fulfill the diagnostic criteria of an ACS, will undergo a 12 weeks treatment period with metyrapone. Metyrapone will be administered with 500 mg at 6 p.m. and 250 mg at 10 p.m., which was previously shown to normalize the circadian cortisol rhythm (10) with only limited risk of an adrenal insufficiency because of the short half-life of the drug.

In these patients, all measurements of WPA will be performed at baseline and after 12 weeks of treatment with metyrapone.

A total of 125 ml blood will be drawn at study inclusion and after 12 weeks of treatment. Therefore, 250 ml blood will be drawn overall during the 3 months study period.

Additionally, to the above-mentioned measurements, the usage of an actimetry watch during the study period will help to monitor the sleep-wake cycles, temperature fluctuations and activity of the individuals to evaluate changes over time.

A clinical evaluation at the endocrine outpatients' clinic will be performed after 2, 4 and 8 weeks of treatment to assess the compliance of study drug intake and clinical tolerance, as well as the need for adaptations in concomitant treatment. Besides blood

pressure, heart rate and body weight, clinical signs of adrenal insufficiency (fatigue, orthostatic hypotension, hypoglycemia) will be recorded systematically. Blood will be drawn only in case of clinical need.

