### **Data Collection**

Data collected at all visits are entered into an interactive form. The CRFs will be source documents verified following guidelines established before study onset as detailed in the Monitoring Plan. Maintenance of the study database will be performed by the designated sub-investigators. Each participant will be assigned to a study specific patient number to ensure anonymity.

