**13. Feasibility**

All study related activities will be performed at the Medical University of Vienna. The Division of Endocrinology has a fully equipped biomedical lab and a human research unit (Outpatient Clinic for Metabolic Research i.e. Outpatient Clinic for Metabolic Research “Chiari”). The access to the MR facility for the non-invasive measurements is warranted in the cooperation with [name]. [name] (MR Centre of Excellence) at the Dep. of Radiology, Medical University of Vienna. There is currently a 3 Tesla Magnetom, scanner available at the MR Centre of Excellence. The system is equipped with suitable software and coils. Performance testing of this setup has been performed extensively in several prior studies (16,21,22). Oral glucose tolerance tests will be performed at the Outpatient Clinic for Metabolic Research “Chiari” of the Division of Endocrinology and Metabolism. MR-studies will take place at the centre of excellence of high-field MR of the Medical University of Vienna. Chronobiology surrogates will be analyzed in cooperation with [name], Platform Rhythms of Life, Center for Molecular Biology and [name], Faculty of Psychology, University of Vienna.

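### The protocol excludes blinding with no exception for outcome reading, so liver-fat spectra and cardiac images may be processed with group and visit known

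*Protocol*

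**What the plan says.** The paragraph on randomization and blinding in section 7 (Study medication) reads "This study is designed as an open label, single armed trial", followed by "No randomization and blinding will be performed". It has no separate provision for those who process outcome data.

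The primary outcome is given as "Hepatic lipid content (HCL) assessed by" proton MR spectroscopy. The secondary outcomes include "Systolic and diastolic heart function, epicardial and pericardial fat mass". On method, Working plan A says "Ectopic fat in the liver, the skeletal muscle and the myocardium will be assessed by the single voxel localized" spectroscopy method on a 3T system. For Working plan B, "all measurements of WPA will be performed at baseline and after 12 weeks of treatment with metyrapone".

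On the setting, section 13 (Feasibility) says "MR-studies will take place at the centre of excellence of high-field MR of the Medical University of Vienna". On coding, section 10 (Data Collection) says "Each participant will be assigned to a study specific patient number to ensure anonymity". Neither statement says what the person processing a scan knows about the patient.

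**The concern.** Leaving treatment open and leaving outcome reading open are separate decisions. Only the first follows from a single-arm drug study. Stored spectra and images can be processed without group or visit labels whatever the patient and the clinician know.

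Single-voxel spectroscopy involves placing a voxel and processing a spectrum. Cardiac function and epicardial or pericardial fat normally involve drawing contours. At each of these steps an expectation can enter, and the protocol states its expectations: section 2 and the sample size calculation anticipate a worse profile in ACS, with HCL about 25% higher, and normalisation on metyrapone.

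HCL is compared twice: between two non-randomised groups (Working plan A) and before versus after treatment in one arm without a concurrent control (Working plan B). In the second comparison the scan date alone reveals treatment state. Masked reading is one of the few protections against bias that this design still allows.

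**Working it through.** The main check is a reading of the protocol, because the plan gives no figure for reader agreement or reading error.

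**Step 1. Is masked reading provided anywhere?**

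| Place in the protocol | What it settles | Does it mask the reading? |
|---|---|---|
| Section 7, randomization and blinding | No blinding, no exception stated | No |
| Section 5, Working plan A | MR method and scanner | Not addressed |
| Section 5, Working plan B | Same measurements at baseline and 12 weeks | Not addressed |
| Section 10, Data Collection | A study number, for anonymity | Not said to hide group or visit |
| Section 10, Periodic Monitoring | CRF entries verified against source documents | No; this would not reveal a shifted contour or spectral fit |
| Section 13, Feasibility | MR site and cooperation | Not addressed |

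The section on eligibility adds that only patients whose hormonal work-up is complete are invited. Group membership is therefore already known when the scan is made.

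**Step 2. What follows?** A team that follows the protocol as written may process scans with group and visit visible. It does not follow that they will, or that results will be biased.

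**Step 3. How much could it matter?** The document cannot answer this. The following is an illustration only, under an assumed systematic reading shift b between the compared sets and no true difference.

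- From the sample size calculation: SD 2.5 percentage points of fat, 25 per group in Working plan A, 15 patients in Working plan B.
- Assumed: b = 0.1, 0.25 or 0.5 points; baseline-to-week-12 correlation r = 0.5 or 0.8; SD 2.5 at both visits; two-sided 5% test; normal approximation.
- Working plan A: SE = 2.5 × √(2/25) = 0.707.
- Working plan B: SE = 2.5 × √(2(1 − r)) / √15, which is 0.645 for r = 0.5 and 0.408 for r = 0.8.
- False-positive rate = 1 − Φ(1.96 − b/SE) + Φ(−1.96 − b/SE).

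| Assumed shift b | Plan A | Plan B, r = 0.5 | Plan B, r = 0.8 |
|---|---|---|---|
| 0.1 | 5.2% | 5.3% | 5.7% |
| 0.25 | 6.4% | 6.7% | 9.4% |
| 0.5 | 10.9% | 12.1% | 23.2% |

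For scale, the expected difference in Working plan A is 25% of 5 = 1.25 points. In Working plan B it is 1.25 if treatment restores the control mean, or 25% of 6.25 = 1.56 if the 25% is taken from the assumed ACS mean. The protocol supports either reading.

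The effect ranges from negligible to material depending on a shift for which the document offers no evidence.

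**Step 4. Does masking alter the design?** No sample-size input changes: 25 per group and 15 patients stay as planned.

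**The case against.** The strongest reply is about scope. The sentence stands under study medication, directly after the description of a single-arm trial. That description fits Working plan B but not the two-group comparison in Working plan A. It may have been meant for treatment only, in which case the protocol is simply silent on readers and an imaging manual might cover the matter. This stands as a limit. A reader might infer that the plan forbids masked reading; the documents do not go that far. But the wording is general, no exception is made, and no masking appears elsewhere in the protocol. Rewording the sentence is useful on either interpretation.

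A second reply is that HCL is an instrument-based quantity, measured at a separate MR centre, on a setup said to have been tested in prior studies, in patients who carry study numbers. It would therefore be wrong to say that nothing in the design limits reader influence. None of these features is masking, however, and the protocol does not say who processes the scans or what they know.

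A third reply is that masked processing cannot reach voxel placement, which happens at acquisition. That is correct. A landmark rule standardises placement without blinding the operator. If the same person acquires and processes the scans, coding and random order reduce recognition but may not remove it.

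Finally, the study calls itself a pilot with exploratory analysis, and masked reading does not cure an uncontrolled before-after comparison. Both are true. They bear on the priority of the change, not on whether it is worth making.

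**Conclusion.** The point holds in a limited form. As written, the protocol excludes blinding without exempting outcome reading and provides masked processing nowhere, so the primary MR outcome and the cardiac images may be processed with group and time point known. This is a cheap improvement, not a defect that invalidates the study.

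The size of any bias cannot be determined from the document. The false-positive rates above rest on assumed shifts and correlations and say nothing about what will happen in this trial.

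Three stronger statements are tempting and unsupported. A reader might infer that the staff do know group and visit; the protocol does not say so. A reader might infer that masking costs nothing; it needs coding work and delays results. A reader might infer that the MR exports are already pseudonymised; the protocol describes pseudonymisation for the actimetry software and a study number for participants, but not how MR files are labelled.

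**What to change.** Replace the blinding sentence in section 7 with wording such as:

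> *Treatment is open label. MR spectra and images are coded without group or visit and processed in random order by the existing MR staff, masked to group and time point, after the last week-12 scan. A technical quality check that does not reveal group or visit is made soon after each scan so that unusable data can be repeated or replaced.*

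Two details matter.

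- **Timing.** The batch must follow the last week-12 scan, not the end of recruitment, because the last patient entered in Working plan B still has 12 weeks to go. If control scans are outstanding then, the batch should wait for those too.
- **Early quality check.** The protocol excludes patients with missing primary outcome data and replaces dropouts. If spectra were first opened in one final batch, unusable ones would be found too late to act on.

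Also define voxel position by anatomical landmark, so that week 12 repeats the baseline location, and state that this standardises acquisition but does not blind it.

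Cost: modest coding work, and no HCL results patient by patient during the study. Masking itself needs no extra patients, visits, scans or readers; a repeat would arise only where a scan is technically unusable.

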## 8. Potential Risks

Metyrapone is a selective inhibitor of the 11-b hydroxylase and is frequently used in the medical treatment of Cushing's syndrome because of its rapid effects (9).

Being generally well tolerated minor, but common side effects include **gastrointestinal side effects** including diarrhea, nausea and vomiting, as well as **fatigue, dizziness and headache**, which are all rapidly reversible after interruption of the drug.

Furthermore, side effects of **hyperandrogenemia** can occur in women, resulting rarely in hirsutism and alopecia. Hyperandrogenemia spontaneously resolves after interruption of metyrapone.

It is important to note that these side effects appear to be largely depending on the daily dose of metyrapone, as well as on the severity of hypercortisolism before treatment of Cushing's syndrome. We therefore assume, that the risk of these side effects is limited in our study, using small daily doses of metyrapone (750 mg per day) in patients with only mild hypercortisolism.

The most dangerous side effect of metyrapone is **adrenal insufficiency**, which can lead to life threatening adrenal crisis in situations of acute stress. Metyrapone is a short-acting steroidogenesis inhibitor and doses given at 6 p.m. and 10 p.m. were shown to lower only cortisol levels in the evening and during the night, without affecting cortisol levels in the morning and afternoon (10). We therefore assume that the risk of adrenal insufficiency is very limited with our treatment regime. However, all study participants will be educated on earliest clinical signs and symptoms of adrenal insufficiency. They will be systematically instructed in the supplementation of Hydrocortisone by tablets in case of the suspicion of an adrenal insufficiency and by subcutaneous injection of hydrocortisone in case of the suspicion of an adrenal crisis. In addition, clinical signs and symptoms of adrenal insufficiency will be assessed systematically at every study visit.

## 9. Safety Definitions and Reporting Requirements

**Summary of known and potential risks of the study drug**

Please find this information provided in the expert information, which will be attached.

**Definition of adverse events**

An AE is any untoward adverse change from the subject's baseline condition, i.e., any unfavorable and unintended sign including an abnormal laboratory finding, symptom or disease, which is considered to be clinically relevant by the physician that occurs during the course of the study, whether or not considered related to the study drug.

Adverse events include:

- Exacerbation of a pre-existing disease.
- Increase in frequency or intensity of a pre-existing episodic disease or medical condition.
- Disease or medical condition detected or diagnosed after study drug administration even though it may have been present prior to the start of the study.
- Continuous persistent disease or symptoms present at baseline that worsen following the start of the study.
- Lack of efficacy in the acute treatment of a life-threatening disease.
- Events considered by the Investigator to be related to study-mandated procedures.
- Abnormal assessments, e.g. physical examination findings, must be reported as AEs if they represent a clinically significant finding that was not present at baseline or worsened during the course of the study.
- Laboratory test abnormalities must be reported as AEs if they represent a clinically significant finding, symptomatic or not, which was not present at baseline or worsened during the course of the study or led to dose reduction, interruption or permanent discontinuation of study drug.

Adverse events do not include:

- Pre-planned interventions or occurrence of endpoints specified in the study protocol are not considered AE's, if not defined otherwise (eg.as a result of overdose)
- Medical or surgical procedure, e.g., surgery, endoscopy, tooth extraction, transfusion. However, the event leading to the procedure is an AE. If this event is serious, the procedure must be described in the SAE narrative.
- Pre-existing disease or medical condition that does not worsen.

- Situations in which an adverse change did not occur, e.g., hospitalizations for cosmetic elective surgery or for social and/or convenience reasons.
- Overdose of either study drug or concomitant medication without any signs or symptoms. However, overdose must be mentioned in the Study Drug Log.

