#### ***Mild***

Event may be noticeable to subject; does not influence daily activities; the AE resolves spontaneously or may require minimal therapeutic intervention;

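### The adverse-event definition makes an undefined judgement of clinical relevance, by a physician who knows the treatment, a condition of entry, so mild symptoms may go unrecorded

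*Protocol*

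**What the plan says.** The general definition in section 9 opens broadly: "An AE is any untoward adverse change from the subject's baseline condition". It then lists signs, symptoms and diseases and restricts them to those in a clause reading "which is considered to be clinically relevant by the physician that occurs during the course of the study". The protocol does not say what makes an event clinically relevant.

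The same subsection has its own thresholds for two kinds of finding. Abnormal assessments "must be reported as AEs if they represent a clinically significant finding that was not present at baseline" or worsened during the study. For laboratory values the rule is: "Laboratory test abnormalities must be reported as AEs if they represent a clinically significant finding, symptomatic or not". Other items in the list of included events carry no such condition, for example "Increase in frequency or intensity of a pre-existing episodic disease or medical condition".

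The mild grade in section 9 reads: "Event may be noticeable to subject; does not influence daily activities". The text under the severe grade adds that even a severe event can have little medical significance, with headache as its example.

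Section 8 introduces the expected effects with "Being generally well tolerated minor, but common side effects include" and names diarrhea, nausea, vomiting, fatigue, dizziness and headache. It then assumes "that the risk of these side effects is limited in our study", because the daily dose is small and the hypercortisolism mild.

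Section 5 (Working plan B) gives metyrapone to 15 patients for 12 weeks. Section 7 states that the trial is open label and single arm.

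**The concern.** Relevance is used here as a condition of entry and not as an attribute recorded after entry. A symptom that the physician considers not relevant is not an adverse event under the general sentence, and nothing requires it to be written down as one. The judgement therefore cannot be reviewed afterwards.

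Such a filter can only take events away. The person applying it knows that the patient takes metyrapone and works under a protocol that already assumes limited side effects. Any error it causes runs towards confirming that assumption. Section 12 describes the trial as a feasibility study that may prepare larger interventional studies, so the tolerability counts from the treated patients are part of what it passes on. Events that were never entered cannot be recovered at analysis.

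**Working it through.** The protocol states no figure on this point, so the main check is a comparison of its sections.

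1. **Reach of the clause.** It follows the list of sign, symptom and disease and is most naturally read as covering all three. Abnormal assessments and laboratory values have a clinical-significance condition of their own, so the general clause adds little there. Its practical effect is mainly on symptoms.
2. **Against the severity grades.** The mild grade describes events that leave daily activities untouched and may resolve by themselves. The text under the severe grade separates intensity from medical significance. The scheme thus expects medically unimportant events to be recorded and graded, whereas the entry rule allows the same events to be turned away.
3. **Against the case report form.** Section 9 (Reporting procedures) lists type, start, end, severity, seriousness, expectedness, outcome and relation to study drug. There is no relevance field.
4. **Against the expected effects and the visit plan.** Of the effects in section 8, fatigue is recorded systematically at the visits of Working plan B, together with orthostatic hypotension and hypoglycemia. Dizziness is covered only in so far as it is picked up as orthostatic hypotension. Nausea, vomiting, diarrhea and headache have no named systematic recording. What the tolerance visits elicit about them becomes an adverse event only through the general definition.

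**Illustration with assumed values.** The protocol gives neither an incidence *p* for any symptom nor the share *f* of cases that would be judged relevant. Both are assumed below; only the 15 patients come from the protocol.

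Expected recorded cases = 15 × *p* × *f*. Probability of recording none = (1 − *p* × *f*)^15.

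| *p* | *f* | Expected cases | Probability of none |
|---|---|---|---|
| 10% | 100% | 1.5 | 20.6% |
| 10% | 50% | 0.75 | 46.3% |
| 20% | 100% | 3.0 | 3.5% |
| 20% | 75% | 2.25 | 8.7% |
| 20% | 50% | 1.5 | 20.6% |
| 20% | 25% | 0.75 | 46.3% |
| 30% | 100% | 4.5 | 0.5% |
| 30% | 50% | 2.25 | 8.7% |

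Worked example: with *p* = 20% and *f* = 50%, 15 × 0.20 × 0.50 = 1.5 cases, and (1 − 0.10)^15 = 0.206. Without a filter, (1 − 0.20)^15 = 0.035. The rows with *f* = 100% are the case in which the clause does no harm. The table shows only that, with 15 patients, a moderate filter would be enough to make a symptom of this frequency disappear from the report fairly often. It does not estimate what will happen.

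**The case against.** A reader might infer that the definition contradicts the mild grade. It does not. Severity and relevance are different axes: a mild event may be judged clinically relevant, and the two texts can be applied together. The case report form provides for mild and for expected events, so these are meant to be entered. What remains is a poor fit between the entry rule and the grading.

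A reader might also infer that tolerability is understated by rule. The text does not support this either. The list of what is not an adverse event does not exclude an event for being mild, and several included categories carry no relevance wording. In section 8, minor describes the common effects by contrast with adrenal insufficiency; it does not call them clinically irrelevant. Because they are named in advance as drug effects, a physician might just as well judge them relevant. The rule gives discretion, and how it will be used is unknown.

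The existing safeguards also count. Visits at weeks 2, 4 and 8 assess clinical tolerance, signs and symptoms of adrenal insufficiency are assessed at every visit, and section 10 (Periodic Monitoring) requires monitors to verify the recording of safety and tolerability endpoints. These narrow the exposure but do not remove it for nausea, vomiting, diarrhea and headache, since a monitor checks against the same definition.

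Finally, adverse events and tolerability are not among the outcomes in section 4, and there is no comparator arm in which ascertainment could differ. The early-termination criterion on adverse events in section 6 concerns serious risk, not mild symptoms. All of this stands and limits the consequence.

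**Conclusion.** The point holds in a limited form. The protocol makes an undefined relevance judgement by an unblinded physician a condition for recording symptoms. This permits under-recording of mild symptoms, chiefly nausea, vomiting, diarrhea and headache, in 15 treated patients. It is a rule that the protocol states, not a detail left to a later document.

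The amount lost cannot be derived from the protocol. It ranges from nothing, if every symptom is judged relevant, upwards with the share turned away; the figures above rest entirely on assumed incidences and shares. The primary outcome and its analysis are untouched. The effect is confined to descriptive safety and tolerability counts. The change is still worth making, because the rule can act in one direction only and the correction is small.

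**What to change.** In the general definition in section 9, remove the relevance clause for signs and symptoms, so that every new or worsened symptom is recorded and then graded. Keep the clinical-significance condition only in the existing items for abnormal assessments and laboratory values. If the investigators want the relevance judgement, add it to the case report form as a field beside severity, so that it describes a recorded event and does not decide whether the event is recorded.

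The cost is one clause, possibly one form field, and a few more mild entries to document in a small group. No dose, visit or clinical rule changes.
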